### Safety aspects

Safety parameters will comprise newly occurring psychiatric diagnoses (LIFE) and all serious adverse events that are reported during and up to six months after treatment.

### Medical complications

The recording of adverse events will be restricted to psychological conditions. Formally, these are defined as any disorder classified by the International Classification of Diseases F00 to F99. A serious adverse eventis an adverse event that may occur at any time of the treatment phase or up to six months after the end of treatment, that: results in death; is life-threatening; requires subject hospitalization or prolongation of existing hospitalization; results in persistent or significant disability or incapacity; or is a congenital anomaly or birth defect.

Any adverse event (according to the study specific definition) reported by the subject or detected by the local investigator will be collected during the trial and must be documented in the CRF. The local investigator will use ICD-10 to code the event. The clinical course of the adverse event will be followed until it has changed to a stable condition or until the end of follow-up phase, whichever comes first. In case of serious adverse events, the Ethics Committee and Data Monitoring Safety Board (DMSB) will be informed within 24 hours of the serious adverse event becoming known.

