**Methods/design:**

Patients are assigned to treatment according to their preference or randomized (if they have no clear preference). Up to 80 sessions of psychodynamic or psychoanalytically oriented treatments (PAT) or up to 60 sessions of CBT are offered during the first year in the study. After the first year, PAT can be continued according to the ‘naturalistic’ usual method of treating such patients within the system of German health care (normally from 240 up to 300 sessions over two to three years). CBT therapists may extend their treatment up to 80 sessions, but focus mainly maintenance and relapse prevention. We plan to recruit a total of 240 patients (60 per arm). A total of 11 assessments are conducted throughout treatment and up to three years after initiation of treatment. The primary outcome measures are the Quick Inventory of Depressive Symptoms (QIDS, independent clinician rating) and the Beck Depression Inventory (BDI) after the first year.

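### Serious adverse events are nested inside a definition limited to F00–F99 disorders, so self-harm, suicide attempts and deaths from other causes need not be recorded or notified

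*Protocol article*

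**What the plan says.** The rule stands in the section Medical complications and is built in four steps.

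1. Scope: "The recording of adverse events will be restricted to psychological conditions".
2. Formal meaning: "these are defined as any disorder classified by the International Classification of Diseases F00 to F99".
3. A serious adverse event is introduced as an adverse event "that may occur at any time of the treatment phase or up to six months after the end of treatment" and that meets one of the usual criteria. These are death, threat to life, hospitalization, lasting disability, and finally "or is a congenital anomaly or birth defect".
4. Collection refers back to step 2: "Any adverse event (according to the study specific definition) reported by the subject or detected by the local investigator will be collected during the trial". Serious adverse events go to the ethics committee and the safety board within 24 hours of becoming known.

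The section Safety aspects names as safety parameters new psychiatric diagnoses from LIFE and "all serious adverse events that are reported during and up to six months after treatment". It gives no wider definition of a serious event.

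On treatment length, the abstract gives PAT as "normally from 240 up to 300 sessions over two to three years". For CBT it gives up to 60 sessions in the first year, extendable to 80, without an end month. The Discussion says that durations across the two treatments range from one to three years, and that CBT will also be extended. Under Secondary analyses, serious adverse events are to be described, not tested.

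**The concern.** The 24-hour route can carry only what the definition lets in. Patients here are chronically depressed, with BDI-2 above 17 and QIDS-C above 10 at entry, and only acute suicidality is excluded. Suicidal acts are the serious events one would foresee in such a sample. A suicide attempt or self-harm is an act, and a fatal physical illness is not a mental disorder. Read literally, the definition requires none of these to be reported. Whether they are seen would then depend on how each local investigator, across several sites, chooses to code.

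A second matter is the length of the serious-event window. It is tied to the end of treatment, and treatment length differs between PAT and CBT. If so, counts of serious events per patient are not comparable between the arms even when the underlying rates are equal.

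**Working it through.** **Definition.** Three kinds of event can be followed through the steps in the protocol.

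- *A new or worsened F-coded disorder that leads to hospitalization.* It is an adverse event, it meets a seriousness criterion, and it is notified.
- *A suicide attempt or self-harm.* If the investigator records the act itself, it is not a disorder in F00–F99. It is then not an adverse event, hence not a serious one, and no notice is due. If the investigator instead records the underlying depressive disorder as the event, with a life-threatening or fatal outcome, it is captured. The text requires neither choice.
- *A death or hospitalization from a physical cause.* There need be no F-coded disorder to record, so the event falls outside at step 2.

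As a consistency check, a congenital anomaly or birth defect is listed as making an adverse event serious, yet the adverse event must be a mental disorder. The criterion does not fit the restriction. This suggests a general list of seriousness criteria was attached to a narrowed adverse event definition without adjusting either.

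**Window.** The protocol states no figure to reproduce. The inputs are:

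- PAT duration of 24 to 36 months (abstract).
- Six months after the end of treatment (Medical complications).
- CBT end not stated; 12, 18 and 24 months are taken as assumptions.

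Window = treatment duration + 6 months. For PAT this is 24 + 6 = 30 to 36 + 6 = 42 months.

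| CBT ends at (assumed) | CBT window | PAT/CBT ratio |
|---|---|---|
| 12 months | 18 months | 30/18 = 1.67 to 42/18 = 2.33 |
| 18 months | 24 months | 30/24 = 1.25 to 42/24 = 1.75 |
| 24 months | 30 months | 30/30 = 1.00 to 42/30 = 1.40 |

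**Illustration in events.** Expected events per 100 patients = 100 × yearly rate × window/12. The rate is an assumption, set equal in both arms. The table takes CBT ending at 12 months.

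| Rate per 100 patient-years | CBT | PAT |
|---|---|---|
| 2 | 3.0 | 5.0 to 7.0 |
| 5 | 7.5 | 12.5 to 17.5 |
| 10 | 15.0 | 25.0 to 35.0 |

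The ratio does not depend on the rate. It depends on when CBT ends.

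**The case against.** The strongest reply to the main point is that death, threat to life and hospitalization are listed as outcomes of an adverse event, not as events needing their own F code. A depressive disorder that worsens and ends in suicide can satisfy both definitions. That is right. A reader might infer that suicides and suicide attempts are excluded by rule, or that an F00–F99 definition cannot hold a fatal event. The text does not support that. It supports only that capture is not required and rests on the investigator's coding.

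Other sources may also show such events. LIFE is held at the main assessments in both arms, hospitalization is part of the relapse definition, and it also enters the health-cost objective. These sources may reveal some events later, but none is a 24-hour notice.

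The ethics committee approved the protocol, and limiting adverse events to psychological conditions is a deliberate choice. For non-serious events that choice can stand. It does not explain why serious events inherit the limit. Nor is this detail that a condensed article leaves to a fuller document, since the article states both the restriction and the nested definition.

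On the window, several objections hold.

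- Only the serious-event window depends on treatment length. Adverse events in general are collected during the trial in both arms.
- Counting serious events on treatment plus a fixed period is a recognizable choice.
- Number and timing of sessions are documented, so exposure can be worked out, and denominators are commonly left to the analysis plan.

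**Conclusion.** The definition is wrong as written and should be amended. Serious events not coded as a mental disorder are not required to be recorded or notified, and for suicidal acts capture is left to coding practice. This conclusion rests on the wording alone and needs no numerical assumption. It does not touch the primary outcome or the efficacy analysis.

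The unequal window is a secondary point. PAT patients are observed for serious events for 30 to 42 months. The ratio to CBT is 1.67 to 2.33 if CBT ends at 12 months, 1.25 to 1.75 at 18 months and 1.00 to 1.40 at 24 months. A reader might take about twofold as the size of the imbalance. That is the case of CBT ending at 12 months, and the abstract and the Discussion both allow CBT to go on longer. A reader might also infer that the planned description will make PAT look less safe. The document says only that serious events are described. It does not say that crude counts will be compared without regard to exposure.

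**What to change.** 1. Apply the F00–F99 restriction to non-serious adverse events only.
2. Define serious adverse events independently of the ICD chapter, and record and notify every event that meets a seriousness criterion. Name death from any cause, suicide attempt and self-harm.
3. Reconcile the sections Safety aspects and Medical complications with this definition, including the list of seriousness criteria.
4. Report serious events per patient-year of observation in each arm.
5. Add a comparison over one window from t0 that is assured in both arms.

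For step 5, t6 (24 months) is the last main assessment that does not depend on funding; t8 (36 months) can serve if it is funded. A window to t6 has two consequences. If CBT ends at 12 months, serious events in CBT must be recorded beyond the present 18 months. The window also leaves out any PAT treatment after month 24 and the six months after PAT. It can therefore only be an added comparison, and all later serious events must still be recorded and notified.

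The cost is an amendment of the definition and the adverse event page of the CRF, some additional serious-event reports, and in CBT possibly some extra months of recording. Design, sample size and primary analysis stay as they are. The article gives recruitment as ongoing, so the change can still act for patients in the trial.

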### Ethical issues

The final study protocol and the final version of the written informed consent form were approved by the Ethics Committee of the Federal State of Rhineland Palatine in Germany (ref: 837.124.075659). The procedure set out in this protocol, pertaining to the conduct, evaluation, and documentation of this trial, were designed to ensure that all persons involved in the trial abide by good clinical practice and the ethical principles described in the current revision of the Declaration of Helsinki. The trial will be carried out in keeping with local legal and regulatory requirements. Before being admitted to the clinical trial, patients must consent to participate after the nature, scope, and possible consequences of the clinical trial have been explained in a form understandable to them. The patients must give written informed consent to participate in the study, including their consent to publish.

## Discussion

This trial has the major goals: (1) to determine the effectiveness of the two long-term treatments (PAT, CBT) reimbursed in the German healthcare system for chronic depression, and (2) to compare the effects of treatment preference against randomization. It combines the virtues of a randomized controlled (efficacy) trial and a naturalistic approach.

As recent meta-analyses have shown, the treatment of depression by short-term treatments has been plagued by high relapse rates and a lack of lasting effectiveness. Long-term PAT and CBT, however, are not easy to compare, as they differ in frequency (one to three sessions per week), total number of sessions, and duration of treatment (one to three years). We therefore tried to reach comparable doses in the first year of treatment. Initially, psychoanalysts often work with low frequency (≤2 sessions per week) with depressed patients; thus there could be 45 sessions of CBT and up to 80 sessions of PAT in the first year. As our primary outcome is measured at one year (t4), doses of treatment can be compared. When psychoanalytic treatment is continued after one year, dose can be adjusted according to patient need and treatment process. As CBT entails relapse prevention, there will also be an extended treatment duration. In any case, number and timing of sessions will be documented. In this trial, a high quality is assured by an independent assessment.

While patient preferences form one of the three key components of evidence-based medicine, studies on the impact of patient preference on outcome have been scarce. Our design enables us to determine the impact of patient preference on outcome, and we expect a lower attrition rate and a higher effectiveness for preferred vs. randomized assignment.

As this trial has been funded substantially by the German Society for Psychoanalysis, Psychotherapy, Psychosomatics, and Depth Psychology (DGPT), a great effort was made to counteract allegiance effects. The study also is financially supported by the independent, medically oriented Heidehof Foundation (part of the well known Robert Bosch Foundation, Stuttgart). One of the principal investigators (MH) is a renowned cognitive behavior therapist. Data collection, monitoring, and analysis are performed by an independent statistician (BR).

## Trial status

Ongoing recruitment.

## Abbreviations

ANCOVA, analysis of covariance; BDI 2, Beck depression inventory II; CBT, Cognitive behavioral therapy; CTQ, Childhood trauma questionnaire; DAS, Dysfunctional attitude scale; DEQ, Depressive Experience Questionnaire; DMSB, Data management and safety board; EU, European Union; HAQ, Helping alliance questionnaire (patient-, therapist-form); HUS, Heidelberger restructuring scale; ICD-10, International classification of diseases, 10th revision; IIP, Inventory of interpersonal problems; LIFE, Longitudinal follow-up evaluation; MDD, Major depressive disorder; OPD-2, Operationalized psychodynamic diagnostics; PAT, Psychoanalytically oriented treatments; PEI, Psychoanalytic Intake Interview; QIDS-C, Quick inventory of depressive symptoms, clinician rating; QIDS-S, Quick inventory of depressive symptoms, self-report; RCT, Randomized controlled trials; SCID I, II, Structured clinical interview according to DSM-IV; SCL-90R, Symptom-checklist; SOFAS, Social functioning; STPP, Short-term psychodynamic psychotherapy; SRS, Self-reflective functioning scale.
